## Abstract

**Background:**

Nutritional status often deteriorates in Alzheimer’s disease (AD). Less is known about whether nutritional care reverses malnutrition and its harmful consequences in AD. The aim of this study is to examine whether individualized nutritional care has an effect on weight, nutrition, health, physical functioning, and quality of life in older individuals with AD and their spouses living at home.

**Methods:**

AD patients and their spouses (aged >65 years) living at home (n = 202, 102 AD patients) were recruited using central AD registers in Finland. The couples were randomized into intervention and control groups. A trained nutritionist visited intervention couples 4–8 times at their homes and the couples received tailored nutritional care. When necessary, the couples were given protein and nutrient-enriched complementary drinks. All intervention couples were advised to take vitamin D 20 μg/day. The intervention lasted for one year. The couples of the control group received a written guide on nutrition of older people. Participants in the intervention group were assessed every three months. The primary outcome measure is weight change. Secondary measures are the intake of energy, protein, and other nutrients, nutritional status, cognition, caregiver’s burden, depression, health related quality of life and grip strength.

**Discussion:**

This study provides data on whether tailored nutritional care is beneficial to home-dwelling AD patients and their spouses.

**Trial registration:**

ACTRN 12611000018910

## Background

Older individuals with Alzheimer disease (AD) living at home with their spouses are an important target group for nutritional care [1] because weight loss and malnutrition are common problem among them [2-4]. Weight loss is a predictive factor of mortality, and it decreases AD patients' and caregivers' quality of life (QOL) [5,6]. Furthermore AD patients often suffer from frailty, sarcopenia, functional impairments, and comorbidities [7]. Their old spousal caregivers often also have comorbidities and functional disabilities [8]. The possibilities of nutritional care in this patient group remain largely unexplored [9].

Nutritional interventions may have beneficial effects on nutritional status and nutrient intake of AD patients [6,10-13]. Several controlled studies have suggested that nutritional supplements increase body weight of AD patients at risk of malnutrition. In an intervention study, weight gain of AD patients was achieved when nutritional supplements were taken for three months [14]. Similarly, Lauque et al. [10] showed that AD patients’ body weight significantly increased with oral nutritional supplements given for three months. A nutrition educational program directed at AD patients and their spouses had a positive effect on AD patients’ weights and their cognitive function [6,13].

However, further studies on the benefits of nutritional care and ways of implementing it are needed [15]. Nutritional care and tailored nutritional counselling are important and largely unexplored means of maintaining the health and QOL of AD patients and their caregivers.

Although nutritional care has been examined and proven effective in randomized, controlled settings in a few multinational studies [1,6,13], the effects of nutritional care on functional ability, health, QOL and use of health services among the aged have not been investigated.

The aim of this study is to investigate whether tailored individualized nutritional counselling and care have an effect on the weight, nutrition, functioning, and QOL of AD patients and their spouses.

## Methods

### General design

This is an intervention trial with a randomized design. The intervention lasts for one year. The intervention group is compared with the control group, who have received a written guide on nutrition of older people. The study has been approved by the Ethics Committee of the Helsinki University Central Hospital and the research committee of KELA (The Social Insurance Institution of Finland). Informed consent has been obtained from each participant and their spousal caregiver before any study procedure.

### Participants

In 2010, a sample of AD patients and their spouses living at the same address in the Vantaa area of Finland was retrieved from the centralized Drug Imbursement Register of the Social Insurance Institution of Finland (KELA). All patients had undergone detailed diagnostic assessments (e.g. cognitive and neuropsychological tests, neuroimaging, and laboratory tests), before receiving reimbursement for their AD medication. The first recruiting letter was sent by KELA with a reply form. Investigators then contacted those who replied. The study purpose and protocol were disclosed to the participants and they were invited to participate. The inclusion criteria were as follows:

 A person with AD living with an aged spouse

 age over 64 years

 being able to use transport (arrive to the study place by taxi)

 being able to stand on a scale

 living in the greater Helsinki area (Helsinki-Espoo-Vantaa)

 adequacy in the Finnish language

 no terminal disease

All AD patients and their spouses showing interest in participation were first contacted and interviewed by phone to confirm the fulfillment of the inclusion criteria. Those couples fulfilling the criteria were invited to the first meeting with a nutritionist, where they were given oral and written information about the study and asked to sign an informed consent. In case of an AD patient’s inability to give informed consent, the spousal caregiver gave proxy consent for both spouses.

### Measurements

The baseline measurements include: background information about demographic data, diagnosis, other potential diseases, falls, fractures, and medication. This information is confirmed from medical records provided by the couples at the first meeting.

The first meeting with baseline measurements takes about two hours. The participants’ (AD patient and spouse) weight, height, and grip strength are measured and body mass index (BMI) is calculated. Weight is measured with a portable, calibrated scale (Dexa).

Both spouses’ nutritional status is assessed by using Mini nutritional Assessment (MNA) [16] and nutritional anamnesis. In addition, the AD patient and the spouse are both assessed by Minimental State Examination (MMSE) [17]. Health-related quality of life (HRQOL) is measured with 15D- HRQOL form [18] and caregiver’s burden with the ZARIT form [19].

The AD patients are assessed by Clinical Dementia Rating Scale (CDR) [20], Neuropsychiatric Inventory (NPI) [21,22], Cornell depression test [23], and Instrumental activities of daily living (IADL) [24] by interviewing the spouse. The spouse is also assessed by IADL. While the spouse is being interviewed, the AD patient has the opportunity to take part in day-time group activities for older people provided by the city of Vantaa in Simonkylä.

A trained nutritionist gives AD patients’ spouses oral and written instructions on how to keep a food diary for three days. They receive food measures of 100 ml, 15 ml, and 5 ml to measure amounts of food items consumed. After investigators receive the completed food diary, the nutritionist checks it and calls the couple to ensure that the amounts of food items, cooking methods, and, for example the type of milk or fat are recorded correctly. The food diaries are analyzed using a Nutrica 3.11 [25] program developed for this purpose.

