### Randomization

The couples are randomized into clusters of six. The randomization is performed as follows: investigators write down identification numbers of each couple on six pieces of papers, which are then folded so that the numbers cannot be seen. A person unrelated to the investigation then chooses three pieces of paper and the couples with these ID numbers are signed to the intervention group.

All participating couples are assessed at baseline and at the end of the trial with methods described previously. In addition, all AD patients’ and their spouses’ weights are measured at six months.

The nutritionist visits and weighs the intervention couples in their homes also at 3 and 9 months. Nutritional counseling and care are tailored according to each intervention couples needs and consists of 4–8 home visits by the nutritionist Table 1.

**Table 1 T1:** Study assessments and timetable

**Assessment**	**Baseline assessments**	**Telephone interview**	**3-month visit**	**6-month visit**	**9-month visit**	**12-month assessment**

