**AD patient**						
Inclusion criteria		x				
Background information^1^	x					x
Nutrition anamnesis	x					x
3-day food diaries^1^	x	x				x
CDR	x					x
MMSE	x					x
MNA	x					x
Weight, BMI	x		x^2^	x	x^2^	x
Grip strength	x					x
NPI	x					x
Cornell	x					x
IADL	x					x
15 D^1^	x					x
Use of health services				x		x

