### Intervention

The nutritionist analyzes the 3-day food diaries recorded by the couples. On the basis of the food diary analysis, MNA, home visits and nutritional anamnesis, the nutritionist develops a plan for individualized nutritional care and discusses nutrition with the couple.

The objective of nutritional care is not to change the AD patients’ and spouses’ food habits completely, but to correct possible inadequacies in their diet. The main objective is to recommend food items that they are familiar with and which are already part of their daily diet. If nutrient deficiencies on the basis of food diaries or further discussions with the spouse are noted that are difficult to correct with food, a supplement is recommended. Nutritional care has the objective of ensuring a sufficient intake of energy, protein, and other nutrients. To increase protein in the diet, good protein sources are recommended, and if the couple seems unable to increase energy, protein, and/or other nutrients in their diet, complementary dietary drinks consisting of protein and other nutrients are given to them for daily use. The complementary drink [Nutridrink protein (200 ml; 300 kcal, 20 g protein) or Nutridrink compact (125 ml; 300 kcal and 12 g protein)] is offered once daily.

All intervention couples are also advised to take 20 μg of supplemental vitamin D daily. The amount of calcium in the diets of participants is also reviewed. The nutritionist visits the couples at least four times and weighs them with a portable scale at 3, 6, and 9 months. At baseline and at the final meeting at 12 months, the weights are also measured along with other assessments. The nutritionist can visit couples’ homes more frequently according to their needs. The intervention couples also receive oral and written advice on exercise to strengthen muscles that is easy to perform at home. The intervention lasts for one year (Figure 1).

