### Outcome

A primary outcome measure is change in AD patients’ weights. Secondary outcomes are changes in their energy, protein, and other nutrient intakes retrieved from food diaries, AD patients’ functional ability [20,24], cognitive functioning (MMSE) [19], neuropsychiatric symptoms (NPI, Cornell) [21-23], and caregiver burden (Zarit burden scale) [17]. In addition, HRQOL [16] and use of health services will be assessed during the on year follow-up.

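### The role that coaches only the intervention couples also checks and corrects the food diaries behind the secondary intake outcomes, and Table 1 omits the 12-month diary call that the text implies

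*Protocol article*

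**What the plan says.** **The diary check.** The Measurements section of the protocol article has the spouse keep a three-day diary. Once it is returned, "the nutritionist checks it and calls the couple to ensure that the amounts of food items, cooking methods" and items such as the type of milk or fat are entered properly.

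**The outcome.** The Outcome section lists among the secondary outcomes changes in the patients' "energy, protein, and other nutrient intakes retrieved from food diaries". The primary outcome is change in the patients' weight.

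**The treating role.** The Intervention section says: "The nutritionist analyzes the 3-day food diaries recorded by the couples". It continues: "On the basis of the food diary analysis, MNA, home visits and nutritional anamnesis, the nutritionist develops a plan for individualized nutritional care". The Randomization section adds: "The nutritionist visits and weighs the intervention couples in their homes also at 3 and 9 months". The aim of this care includes adequate energy and protein intake. Control couples receive a written guide.

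**Timing.** The Randomization section says: "All participating couples are assessed at baseline and at the end of the trial with methods described previously". In Table 1 the diary row is ticked at baseline, under "Telephone interview" and at 12 months, for both patient and spouse. No telephone contact is shown with the 12-month assessment.

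**The concern.** A telephone check of portions and cooking methods depends on judgement: the caller decides which entries to query, how hard to press, and what to change. At 12 months the role making the call knows which couples received a care plan and what that plan asked for, because it wrote the plan and made the visits. If entries are queried differently in coached and uncoached couples, the two arms' intake data are no longer produced in the same way, and part of any difference in intake could come from the editing.

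Intake is what the counselling sets out to change, so readers will look to it to judge whether the intervention worked as intended. A biased intake comparison could suggest a dietary effect that did not occur, or hide one that did.

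There is also a documentation problem. The text implies a diary call at 12 months and Table 1 does not show one, so staff working from the table and staff working from the text could handle the final diary differently.

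**Working it through.** The article gives no figure for diary error, so the main check is a comparison of its statements.

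**1. Who edits, and who treats.** Measurements gives the diary call to the nutritionist. Randomization and Intervention give the nutritionist the home visits, the diary analysis and the care plan, in the intervention arm only. The article names no other role for checking diaries. That one individual does both is inferred from the shared role name and is not stated.

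**2. Is there a 12-month call?**
- The sentence in Randomization covers all couples and refers back to the methods already described, which include the call. On a plain reading, the call is made at 12 months in both arms.
- Table 1 has one telephone column, placed between baseline and 3 months. The same column holds the inclusion-criteria check, which the Participants section puts before the first meeting. The column's position therefore does not date the diary call.
- The diary tick carries only the footnote for forms filled in at home, not the one for the intervention group alone. Nothing limits the call to one arm.

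Table 1 and Randomization are thus not aligned, but the table does not establish that the call happens only at baseline.

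**3. What follows under each reading.**
- *Call made at 12 months in both arms:* the final record passes through an edit by a role that knows the allocation. Differential bias between arms is possible.
- *No call at 12 months in either arm:* the method changes between baseline and follow-up. That shifts the change within each arm. It does not by itself bias the difference between arms, provided the baseline check was done alike in both.

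The bias concern therefore belongs to the first reading, which is the one the text supports.

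**4. Effect on the primary outcome.** Weight comes from a scale, not a diary. The Statistical analyses section uses SD 3.6 kg, difference 2 kg, type I error 5% and power 80%. The normal-approximation formula, two-sided, gives:

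n = 2 × (1.96 + 0.84)² × 3.6² / 2² ≈ 50.9, so 51 per group.

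The stated 50 agrees closely (power 79.3% at 50). This calculation is unaffected by the diary step.

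**5. Illustration of size, under assumption.** Let b be a between-arm recording bias in units of the SD of intake change, with no true effect, 50 patients per arm and a two-sided 5% t-test. The noncentrality is b × √(50/2) = 5b.

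| Assumed b | Noncentrality | Chance of a significant result |
|---|---|---|
| 0.1 | 0.5 | 7.9% |
| 0.2 | 1.0 | 16.8% |
| 0.3 | 1.5 | 31.8% |
| 0.4 | 2.0 | 50.8% |
| 0.5 | 2.5 | 69.7% |

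Without bias the figure is 5%. Nothing in the article says which row, if any, applies. The table shows only that a modest bias would matter at this sample size.

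**The case against.** The strongest defence has five parts.

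- **Table 1.** A reader might infer that the call is scheduled only at baseline, so that a corrected first diary is compared with an uncorrected last one. The documents do not support this. The telephone column also holds an eligibility call made before baseline, and Randomization carries the methods to the end of the trial. This defence stands in full. What remains is a mismatch to be tidied.
- **Direction.** A reader might infer that the call raises recorded intake in the coached arm. The article describes a factual check, and a correction can lower a figure as easily as raise it. This stands too: the direction is unknown.
- **Condensation.** Call scripts and masking are details that an article may leave to the full protocol. This stands for a missing script taken alone. It does not answer the point, which rests on what the article does state: it describes the diary procedure closely and gives the call to the treating role.
- **Stakes.** Intake is secondary, the secondary outcomes are not ranked, and no planned analysis uses intake to explain the weight result. This stands and limits the weight of the point.
- **Remedy.** Recruitment is complete, so many baseline diaries have probably been corrected already, and a script does not mask a caller who knows the couples. This stands as a limit on what the fix can achieve.

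**Conclusion.** The point holds for the secondary intake outcomes only. As described, they pass through a judgement-dependent edit by the role that counsels one arm on those same nutrients, and the text implies this edit at 12 months in all couples. The intake comparison is therefore open to differential measurement bias of unknown size and direction. Weight and the sample size are not affected.

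The conclusion rests on two readings: that the Randomization sentence includes the diary call, and that the shared role name means the checker knows the allocation. If a separate, unaware person makes the 12-month call, the bias concern largely falls away. If no 12-month call is made in either arm, within-arm change is distorted, but the between-arm comparison is not biased by that alone.

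Separately, Table 1 and the Randomization section should be reconciled on whether the final diary is followed by a call.

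**What to change.** - State in the text and in Table 1 that the diary call is made after both the baseline and the 12-month diary, in both arms.
- Make the call from one fixed, arm-neutral script covering amounts, cooking method, and milk and fat type. Log every change.
- Keep the as-received diary as a separate coded version, for all outstanding 12-month diaries and for baseline wherever the uncorrected record survives.
- Use the scripted, corrected version as the outcome. Repeat the between-arm comparison on the as-received version as a sensitivity analysis, and report both.

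The Trial status section says follow-up is still running, so this can be applied to 12-month diaries not yet collected.

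**Cost:** a short script, a little extra data entry and one more analysis, with no new staff. If no 12-month call is already planned, it adds one call per couple.

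**Limits:** the caller is still not masked, and spouses who know their allocation may still report differently. The gain is that the editing is uniform and its influence on the result can be seen.

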### Randomization

The couples are randomized into clusters of six. The randomization is performed as follows: investigators write down identification numbers of each couple on six pieces of papers, which are then folded so that the numbers cannot be seen. A person unrelated to the investigation then chooses three pieces of paper and the couples with these ID numbers are signed to the intervention group.

All participating couples are assessed at baseline and at the end of the trial with methods described previously. In addition, all AD patients’ and their spouses’ weights are measured at six months.

The nutritionist visits and weighs the intervention couples in their homes also at 3 and 9 months. Nutritional counseling and care are tailored according to each intervention couples needs and consists of 4–8 home visits by the nutritionist Table 1.

**Table 1 T1:** Study assessments and timetable

**Assessment**	**Baseline assessments**	**Telephone interview**	**3-month visit**	**6-month visit**	**9-month visit**	**12-month assessment**
**AD patient**						
Inclusion criteria		x				
Background information^1^	x					x
Nutrition anamnesis	x					x
3-day food diaries^1^	x	x				x
CDR	x					x
MMSE	x					x
MNA	x					x
Weight, BMI	x		x^2^	x	x^2^	x
Grip strength	x					x
NPI	x					x
Cornell	x					x
IADL	x					x
15 D^1^	x					x
Use of health services				x		x
**Spouse**						
Background information^1^	x					x
Nutrition anamnesis	x					x
3-day food diaries^1^	x	x				x
Zarit^1^	x					x
MNA	x					x
MMSE	x					x
15 D HRQOL^1^	x					
IADL	x					x
Weight, BMI	x		x^2^	x	x^2^	x
Grip strength	x					x
Use of health services				x		x

^1^filled at home.

^2^only in intervention group.

*AD *Alzheimer’s disease, *CDR *degree of dementia [20], *MMSE *Mini mental state examination [17], *MNA *Mini Nutritional Assessment [16], *BMI *body mass index, *NPI *Neuropsychiatric inventory [21,22], *Cornell *depression test [23], *IADL *Instrumental activities of daily living [24], *15 D *HRQOF [18], *Zarit *Zarit burden scale [19].

### Intervention

The nutritionist analyzes the 3-day food diaries recorded by the couples. On the basis of the food diary analysis, MNA, home visits and nutritional anamnesis, the nutritionist develops a plan for individualized nutritional care and discusses nutrition with the couple.

The objective of nutritional care is not to change the AD patients’ and spouses’ food habits completely, but to correct possible inadequacies in their diet. The main objective is to recommend food items that they are familiar with and which are already part of their daily diet. If nutrient deficiencies on the basis of food diaries or further discussions with the spouse are noted that are difficult to correct with food, a supplement is recommended. Nutritional care has the objective of ensuring a sufficient intake of energy, protein, and other nutrients. To increase protein in the diet, good protein sources are recommended, and if the couple seems unable to increase energy, protein, and/or other nutrients in their diet, complementary dietary drinks consisting of protein and other nutrients are given to them for daily use. The complementary drink [Nutridrink protein (200 ml; 300 kcal, 20 g protein) or Nutridrink compact (125 ml; 300 kcal and 12 g protein)] is offered once daily.

All intervention couples are also advised to take 20 μg of supplemental vitamin D daily. The amount of calcium in the diets of participants is also reviewed. The nutritionist visits the couples at least four times and weighs them with a portable scale at 3, 6, and 9 months. At baseline and at the final meeting at 12 months, the weights are also measured along with other assessments. The nutritionist can visit couples’ homes more frequently according to their needs. The intervention couples also receive oral and written advice on exercise to strengthen muscles that is easy to perform at home. The intervention lasts for one year (Figure 1).

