## Discussion

This intervention trial investigates the effect of individualized, home-based tailored nutritional care on home-dwelling AD patients and their aged spouses. A nutritionist visits the intervention couples in their homes 4–8 times according to their nutritional needs. In addition, the intervention group is given oral and written counseling on exercise and how to perform daily exercise routine to strengthen muscles. If the intervention couple is unable to complement their diet naturally and clear deficiencies in protein and/or other nutrients are observed, the couple will be given complementary daily drinks that contain energy, protein, and other nutrients. Dietary supplements are recommended to AD patient and spouse when necessary. In addition, intervention couples are advised to take a 20 μg vitamin D supplement daily year round. The control group is given a written guide on nutrition of the older people.

Our study has several strengths. All AD patients have an established diagnosis of AD; they were recruited from the Finnish drug registry. As AD is a risk factor for deterioration of nutritional status, this intervention enables this problem to be dealt with at early stage of the disease. Old spouses also often have multiple diseases and disabilities, and thus, are an important target group for nutritional care. Tailored nutritional care may enable the aged couple to live in their home longer. Findings of this trial are directly applicable to real life, allowing nutritionists and healthcare professionals to focus on nutritional interventions for the older people. Tailored nutritional intervention that addresses the nutritional needs of AD patients and their caregivers is described in detail.

The study also has potential drawbacks. First, our study population is old and frail with many comorbidities, thus, being vulnerable to various complications. Second, a sufficient difference may be difficult to obtain between intervention and control groups. Contamination of the control group is probably not a problem because home-based nutritional interventions are not available in Finland to AD patients and their spouses.

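### Only the intervention arm is described as getting strength-exercise advice, so effects on grip strength and function belong to the package and cannot be credited to nutritional care alone, as the aim and conclusion imply

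*Protocol article*

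**What the plan says.** Two places in the protocol article describe the exercise component. The Intervention section states: "The intervention couples also receive oral and written advice on exercise to strengthen muscles that is easy to perform at home". The Discussion, summarising what the arm receives, repeats it as an addition to the home visits: "In addition, the intervention group is given oral and written counseling on exercise and how to perform daily exercise routine to strengthen muscles". It is therefore a planned element for all intervention couples.

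For controls, General design says: "The intervention group is compared with the control group, who have received a written guide on nutrition of older people". The Discussion agrees: "The control group is given a written guide on nutrition of the older people". Nowhere is exercise advice described for them.

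The research question, at the end of the Background, is "whether tailored individualized nutritional counselling and care have an effect on the weight, nutrition, functioning, and QOL of AD patients and their spouses". The closing statement of the abstract is: "This study provides data on whether tailored nutritional care is beneficial to home-dwelling AD patients and their spouses". The abstract's Methods paragraph lists home visits, tailored care, drinks when needed and vitamin D, and does not mention exercise.

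Weight change in the AD patients is primary. The Outcome section lists functional ability and HRQOL among the further outcomes. The abstract adds grip strength as a secondary measure, and Table 1 schedules it at baseline and 12 months for patient and spouse.

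**The concern.** The question is about one kind of treatment and the randomised contrast contains two. Advice meant to strengthen muscles is aimed directly at something the trial measures (grip strength) and plausibly reaches another (functional ability). If the intervention arm does better on these, the abstract's intended conclusion would credit nutritional care for a result that the exercise advice may have produced in part or in whole.

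The omission in the abstract makes this worse for readers: someone relying on it would not know that exercise advice was part of the intervention. The drawbacks in the Discussion do not alert them either. They cover frailty and the difficulty of achieving a sufficient difference, and they discount contamination only with regard to nutritional interventions. At stake is what the trial may conclude, not whether the comparison is fair.

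**Working it through.** This is a question of design, so most of the check is a side-by-side reading.

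| Element | Intervention arm | Control arm | In aim and intended conclusion? | In abstract's Methods? |
|---|---|---|---|---|
| Tailored nutritional care, home visits | yes | no | yes | yes |
| Complementary drinks when needed, vitamin D advice | yes | not described | yes, as part of nutritional care | yes |
| Nutrition group meeting (optional) | yes | not described | yes, as part of nutritional care | no |
| Oral and written strength-exercise advice | yes | not described | **no** | **no** |
| Written nutrition guide | not described | yes | comparator | yes |

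Exercise advice is the one row that differs between arms and falls outside the stated question. The group meeting is about nutritional issues, so it belongs to nutritional care and is not a second type of treatment.

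**What the contrast estimates.** Let N be the effect of nutritional care on an outcome and E the further effect of adding the exercise advice. The difference between arms estimates N + E. With three of every six couples allocated to intervention, 102 patients give 102 × 3/6 = 51 per arm: 51 planned to receive both components and 51 described as receiving neither. No group receives one without the other, so N and E cannot be estimated separately from the arm comparison.

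**The plan's own figure.** With SD 3.6 kg, difference 2 kg, two-sided α of 5% and 80% power:

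n per arm = 2 × (1.960 + 0.842)² × 3.6² / 2² ≈ 50.9, rounded up to 51.

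The plan states 50 per group, where power is 79.3% by the same normal formula, so the figure reproduces. It concerns the total difference between arms and is untouched by this point.

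**Illustration for weight.** The documents give no exercise effect on weight, so the values of E below are assumptions and show only how the test behaves. Take N = 0, 51 per arm and SD 3.6 kg. The standard error is 3.6 × √(2/51) ≈ 0.713 kg. The chance of a significant two-sided result is Φ(E/0.713 − 1.96) + Φ(−E/0.713 − 1.96):

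| Assumed E (kg) | Chance of p < 0.05 with no nutrition effect |
|---|---|
| 0.25 | 6.4% |
| 0.5 | 10.8% |
| 1.0 | 28.9% |

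By symmetry, the same chances apply for E of the opposite sign, with the significant results then mostly in the other direction. These figures are not evidence that exercise advice moves weight by any of these amounts.

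**Exposure by outcome.** Grip strength is most exposed, then functional ability; HRQOL is less certain. For weight, size and direction are unknown. Energy, protein and other nutrient intakes from food diaries are little exposed.

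**The case against.** The strongest reply is that this is a disclosed, pragmatic package. The exercise advice appears under Intervention and again in the Discussion, the authors want findings applicable to real life, and bundling is a legitimate choice. Drinks, vitamin D and counselling cannot be separated from one another either. This stands as far as validity goes: the randomised comparison is sound for the package. It does not settle the labelling, because drinks, vitamin D and counselling all fall under nutritional care and exercise advice does not.

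A second reply is that advice described as easy to do at home, with no supervised training or stated dose, may do little. That is possible, and the documents show no effect of it on any outcome. The point needs only that the aim and conclusion leave out a component given to one arm; it does not need the component to be potent.

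Third, an article condenses the full protocol. Recording of exercise, and the content of the control guide, may be set out elsewhere. So the absence of an exercise row in Table 1 is not a finding here, and that controls get no exercise advice is a reasonable inference from their description, not a stated fact.

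A reader might go further and infer that the trial fails to answer its question, or that its weight result would be uninterpretable. The documents do not support that. No size or direction is given for an exercise effect on weight, and intake is measured by food diary in both arms at baseline and 12 months, so a weight effect can be read against changes in intake.

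**Conclusion.** The point holds as one of attribution. The trial validly estimates the effect of tailored nutritional care plus home strength-exercise advice against a written nutrition guide. It cannot assign effects on grip strength and functional ability, and less certainly HRQOL, to nutritional care alone, although the aim and intended conclusion do so. For weight the claim goes no further than that an exercise contribution of unknown size and sign is included in the difference.

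The mismatch covers the whole intervention arm, about 51 of 102 patients, and the share due to exercise cannot be estimated from the randomised contrast. This rests on two assumptions: that the control guide deals with nutrition only, as it is described, and that the advice is delivered to all intervention couples, as both sections say. Confidence is high on the difference between arms and the wording, and low on how large any exercise effect would be.

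**What to change.** Before results are known:

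- Restate the aim, the abstract's description of the intervention and the planned conclusion as tailored nutritional care plus home strength-exercise advice versus a written nutrition guide.
- Add to the drawbacks in the Discussion that effects on strength, function and quality of life will not be credited to nutrition alone.

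Recruitment is complete and follow-up continues, so this can be done without touching either arm's treatment, the sample size or the analysis.

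A question on home strength exercise, put to both arms at the existing 12-month assessment, is optional. It would describe uptake only. It is retrospective, measured after randomisation and possibly answered by proxy, so it cannot separate the two components and should not be used to adjust the comparison.

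The cost is some rewording and a narrower claim.
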